#### Study participants

2.3.3

All health workers will be screened for eligibility based on the following inclusion criteria^[5,18,19]^:

i.Health workers employed as accredited social health activistsii.Health workers living within a radius of 40kms from the identified health centers.

The exclusion criteria are:

i.Pregnant health workersii.Health workers unwilling/unable to provide written informed consent.iii.Health workers with terminal illnesses.

#### Sampling method

2.3.4

Cluster sampling method will be utilized for the study. First, 8 health centers will be chosen from the Hyderabad & Rangareddy districts and will further be then randomized as clusters into either the intervention or the control arms. All health workers at the respective clusters will be included in the respective arms based on their eligibility and consent.

A total of approximately 294 health workers will participate in the study, encouraged both by getting continuing education and by being urged by a district health officer to participate. We expect that approximately 147 health workers will enter the intervention arm, wherein they will participate in 20 hours of the intervention to be considered as trained. Evidence shows that even brief interventions have an impact on effective knowledge.^[36]^ The principal investigator and the field staff will take the requisite permission form authorities and enroll the participants into the study based on their consent, which will be recorded using a consent form.

To prevent possible confounding and effect modification of patients’ characteristics, we will divide the health centers into pairs. The pairs will have the following characteristics: male/female ratio, percentage of patients ≥ 60 years old, percentage of patients on treatment and the prevalence of patients suffering from chronic diseases. The centers will be then randomly allocated into an experimental group and a control group and will be compared to ascertain the balance of the allocation. This will be done using computer generated random number using the MS Excel software. Pre- and postassessment scores will be recorded at baseline and at after the intervention. These scores will serve as the data regarding competence assessment. Health workers’ characteristics will be not included in the randomization process. This data is not available prior to the information from the baseline questionnaire being received (Fig. 1 emphasizes the relationship, being examined in the evaluation). The intervention is randomized and is hence an important variable between exposure and outcome in the experimental group as well as the evaluation method (e.g., before and after study). Concurrently potential confounders will also be identified and would majorly consist of health workers’ characteristics.

**Figure 1 F1:**
[figure not shown]
Primary Hypothesis displaying intervention, intermediate and outcome of interest.

### Intervention

2.4

#### Implementation of intervention

2.4.1

The implementation of the intervention package consists of training of health workers and evaluation of the training on the clinical competence of the health workers undergoing the training. The intervention will be implemented in the following manner:

1.Identification & Selection of health centers2.Needs assessment of important stakeholders to improve the efficacy of the subsequent training3.Development of Intervention package and its validation4.Identification & recruitment of health workers for study5.Delivery of Intervention package:a.Health worker Training: The first part of the package will focus on the training of the health workers in the intervention arm.b.Evaluation of training: The second part of the package will focus on the evaluation of the training. This will be done using the questionnaire tool developed for pre and post-session and pre and post-intervention evaluation of the theoretical competence. An additional practical evaluation will be conducted by a neutral doctor to assess that change in clinical competence. The evaluation mechanism will be identical in both the control and the intervention arms (Fig. 2 showcases the overview of the intervention).

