### Study design

2.3

We will conduct a 12 months prospective, unblinded, parallel cluster randomized controlled trial. The study will measure changes in healthcare worker competence levels related to type 2 diabetes mellitus and complications. The health centers chosen as the clusters will be then randomized into intervention and control arms. The health workers at the respective health center will be thus assigned to the respective cluster arm. The clusters will be chosen such that they are geographically distinct. This will avoid any possible contamination within the groups. Health workers in the control group will continue to deliver services according to the current standards and guidelines.^[28,30,31,35]^ The intervention group participants will undergo additional training. This will be spread over six months and delivered for 20 hours.^[36]^ It will entail pre and post-assessment questionnaires and practical assessments as the modality of evaluation.

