#### Training of health workers

2.4.2

The HWs in the intervention arm will then undergo the customized training. The training module will include the following topics^[3,28]^:

NCD's and their prevalence in rural areasImportance of prevention, early detection and managementDiabetes and its prevalence in India and rural IndiaDiabetes Pathogenesis,Signs and symptoms and basic pathology of diabetesCommon drugs used, Insulin,Importance of self-management,Key Skills- Using risk assessment tools, generating awareness history taking, behavior counselingScreening, Measurement of blood glucose (using glucometer)Complications-∘Hypoglycemia∘Wound and ulcers in diabetes∘Oral complication of diabetes∘Diabetic Foot∘Diabetic Nephropathy∘Diabetic Retinopathy, etc.Follow-up & its importance: Motivation for follow-up, Motivation & Support for lifestyle changes, community meetings, patient support groups, continuity of careIndian Health System and approach to primary care.

The module will be collated using the available modules which were developed and published by the Ministry of Health and Family Welfare, Government of India, Indian Council of Medical Research operational guidelines, The National Program for Prevention and Control of Cancer, Diabetes, Cardiovascular diseases and Stroke operational guidelines and literature from Indian Institute of Public Health-Hyderabad & Public Health Foundation of India.

After the 6-month training phase, an evaluation will occur. The evaluation will consist of theoretical and practical components which will be conducted using the developed questionnaire and the same set of trained public health experts respectively. The same tools would also be used for baseline collection. Both of these techniques will help assess the change in effective knowledge as well the practical skills about type 2 diabetes mellitus & associated complications. The detailed training plan is described below:

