### Data collection, management & analysis

2.5

All the data will be collected from both the arms at pre-specified intervals. Pre and post- intervention data will be collected from the control arm. In the intervention arm, pre and post- training data will be collected, at the baseline and after the intervention is concluded. Hence evaluation will be conducted across both the groups at identical time points to obtain an accurate comparison of the training imparted. Qualitative and quantitative data will be collected during and after the intervention. The collected data will be coded and recorded in Microsoft Excel version 2020 (MS Excel). We will use MS Excel for summarizing the descriptive statistics.

These will be obtained from the socio-demographic characteristics, socioeconomic characteristics, lifestyle characteristics, type 2 diabetes screening, health center visits for physician follow-up and health center visits for medicine refill. We will use STATA for data analysis. The principal analysis strategy will be the use of linear mixed models using the R statistical package for computing. This approach provides a simple method to incorporate baseline values and the correlation of each participant over time (using a random effect). This model is more potent than the repeated measures analysis of variance. It can easily examine differences between the trial groups at all time points and can accommodate potential confounders. Subsequent adjustments will be made for potential confounding variables as necessary, such as baseline parameters that may vary between groups.

Data on the confounding factors including sex, literacy, distance from the health centre, marital status will be collected at baseline. Other socio-demographic details, socioeconomic status, and occupation will also be recorded at baseline.

Secondary contrasts will be used to examine differences from baseline for all other time points. However, these will be of exploratory interest only.

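### One questionnaire tool is assigned to both session tests and the outcome test, so the intervention arm may meet outcome items more often than controls

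*Protocol article*

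**What the plan says.** Section 2.4.1 (Implementation of intervention) says that theoretical competence will be evaluated "using the questionnaire tool developed for pre and post-session and pre and post-intervention evaluation of the theoretical competence". One tool, in the singular, thus serves two levels of testing. The same item of the list ends: "The evaluation mechanism will be identical in both the control and the intervention arms".

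The arms differ in whether they have sessions at all. Under Study design (2.3), "The intervention group participants will undergo additional training", and of that training, "This will be spread over six months and delivered for 20 hours". For controls, "Health workers in the control group will continue to deliver services according to the current standards and guidelines".

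Section 2.5 sets out the data collection. For controls: "Pre and post- intervention data will be collected from the control arm". For the intervention arm, "pre and post- training data will be collected, at the baseline and after the intervention is concluded". It concludes that both groups are evaluated on the same occasions and does not mention session tests. Section 2.4.2 says of the tools used for the final evaluation: "The same tools would also be used for baseline collection". Section 2.4.3 (Evaluation) describes an overall pre- and post-test questionnaire for both arms, to be combined with a practical score.

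**The concern.** A test given before and after a training session can be given only to workers who attend sessions. If those tests draw on the outcome questionnaire, one arm answers outcome items at baseline, around the teaching of the relevant content, and again at the end. The other arm answers them at baseline and end only.

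The aim is to change competence in type 2 diabetes, not recall of particular questions. Practice from the two shared occasions should largely cancel between arms. Practice from additional occasions would not, because it coincides with allocation. The linear mixed model in section 2.5 uses baseline values and a participant random effect. Neither removes an influence that arises after baseline and in one arm only. Part of the estimated training effect on the paper score could then be item familiarity, and nothing in the collected data would show how much.

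**Working it through.** **Step 1: the passages side by side.**

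| Section | Intervention arm | Control arm |
|---|---|---|
| 2.3 | training over six months, 20 hours | usual service |
| 2.4.1 | one tool for session and pre/post-intervention tests | no sessions; evaluation said to be the same as in the other arm |
| 2.4.2 | same tools at baseline and after training | no separate statement |
| 2.4.3 | overall pre/post questionnaire plus practical test | the same |
| 2.5 | baseline and end | pre and post |

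Sections 2.4.3 and 2.5 fit symmetric testing. Section 2.4.1 adds session tests with the same tool. It is consistent with identical evaluation only if the session tests share no items with the outcome form, or are not given. The article states neither.

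**Step 2: reproduce the plan's own figure, to fix the precision.** Inputs from section 2.3.2: z values 1.96 and 0.84, d = 0.5, m = 30, ρ = 0.03, dropout 20%.

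- Unadjusted: 2 × (1.96 + 0.84)² / 0.5² = 62.72 per arm.
- Design effect: 1 + (30 − 1) × 0.03 = 1.87.
- Product: 62.72 × 1.87 = 117.3; the plan states 117.
- Dropout: 117 / 0.8 = 146.25, rounded up to 147 per arm and 294 in total, as stated.

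The plan's figures reproduce, and this point does not change them.

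**Step 3: standard error of the arm difference, in SD units.** With 117 analysed per arm:

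SE = √(2 × 1.87 / 117) = 0.179.

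**Step 4: illustrative consequence.** Let b be the shift in the combined score caused by extra exposure alone, with no true training effect. The documents give no value for b, so 0.1 to 0.3 SD is an assumption. The rejection probability of a two-sided 5% test follows from b / SE. The main reference is a noncentral t with 6 df (8 centres minus 2 arms, ignoring the pairing in section 2.3.4). A normal test is shown for comparison.

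| b (SD) | b / 0.5 | Rejection, t on 6 df | Rejection, normal |
|---|---|---|---|
| 0 | 0% | 5.0% | 5.0% |
| 0.1 | 20% | 7.6% | 8.7% |
| 0.2 | 40% | 15.8% | 20.1% |
| 0.3 | 60% | 29.4% | 38.9% |

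**Step 5: dilution by the practical score.** Section 2.4.3 combines paper and practical scores without stating weights. Assume equal weights on standardised scores with correlation r. A paper shift of p SD then moves the combined score by (p/2) / √((1 + r)/2) = p / √(2(1 + r)) SD. The paper shift needed is therefore b × √(2(1 + r)):

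- b = 0.1 needs 0.14 SD (r = 0) to 0.20 SD (r = 1).
- b = 0.2 needs 0.28 to 0.40 SD.
- b = 0.3 needs 0.42 to 0.60 SD.

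The upper rows of the table in step 4 therefore require a sizeable practice effect on the paper test.

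**The case against.** The strongest case against is that the clause in section 2.4.1 need not mean that the same items are reused.

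- Sections 2.1.1 and 2.3 speak of questionnaires in the plural.
- Section 2.4.3 calls the outcome form the overall questionnaire, which suggests that session tests are something else.
- Section 2.5 lists only baseline and end for the intervention arm too.
- The training-schedule table and the overview figure, where session tests might be set out, are not shown here.
- An article may leave the allocation of items to the full protocol.

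Much of this stands. A reader might infer that the intervention arm rehearses the full outcome instrument for six months. The article does not say so: it gives neither the content nor, in readable text, the number of session tests. Section 2.4.2 places a trainer support session at three months, after three meetings. That hints at about six meetings but does not establish how many tests there are. Nor does the article say that trainers see the outcome items, or tie the practical assessment to session testing. A reader might also take 16% to 29% as the trial's actual false-positive rate. Those figures rest entirely on an assumed shift of 0.2 to 0.3 SD, and at 0.1 SD the rate is close to nominal.

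The objection does not remove the clause. No section separates session items from outcome items, and section 2.4.1 positively assigns one tool to both uses. Topic subsets of that tool would still expose outcome items in one arm only. This is therefore a matter of what the article states, not of detail it leaves out.

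**Conclusion.** The point holds as a limited one. As worded, section 2.4.1 allows the intervention arm more contact with outcome items than the control arm, which conflicts with its own statement that evaluation is identical in both. Any resulting bias would favour the intervention if familiarity raises scores. It would enter through the paper part of the combined score and could not be removed by the planned model.

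Its size is unknown. As an illustration, a shift of 0.1, 0.2 or 0.3 SD in the combined score would equal 20%, 40% or 60% of the planned d = 0.5. With no true effect it would give about 8%, 16% or 29% rejection instead of 5%. This assumes 117 analysed per arm, ρ = 0.03, a design effect of 1.87 and a t reference on 6 df. It is not shown that rehearsal of the whole instrument is planned. The change is worth making because it is cheap and the tool has not yet been built.

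**What to change.** Make sections 2.4.1, 2.4.3 and 2.5 say the same three things:

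1. Tests given before and after training sessions use items separate from the outcome questionnaire.
2. The outcome questionnaire is given only at baseline and at the end of the intervention, in both arms.
3. Session scores are training process data and do not enter the competence outcome.

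The cost is some extra item writing during tool development. Section 2.1.1 still has the questionnaire to be developed and validated with 30 health workers, so this can be done then. No visits are added and the sample size is unchanged. Parallel forms of the outcome questionnaire for baseline and end are optional: they would need equating, and reserving the items already removes the difference in exposure between arms.

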**Figure 2 F2:**
[figure not shown]
Overview of the intervention.

#### Training of health workers

2.4.2

The HWs in the intervention arm will then undergo the customized training. The training module will include the following topics^[3,28]^:

NCD's and their prevalence in rural areasImportance of prevention, early detection and managementDiabetes and its prevalence in India and rural IndiaDiabetes Pathogenesis,Signs and symptoms and basic pathology of diabetesCommon drugs used, Insulin,Importance of self-management,Key Skills- Using risk assessment tools, generating awareness history taking, behavior counselingScreening, Measurement of blood glucose (using glucometer)Complications-∘Hypoglycemia∘Wound and ulcers in diabetes∘Oral complication of diabetes∘Diabetic Foot∘Diabetic Nephropathy∘Diabetic Retinopathy, etc.Follow-up & its importance: Motivation for follow-up, Motivation & Support for lifestyle changes, community meetings, patient support groups, continuity of careIndian Health System and approach to primary care.

The module will be collated using the available modules which were developed and published by the Ministry of Health and Family Welfare, Government of India, Indian Council of Medical Research operational guidelines, The National Program for Prevention and Control of Cancer, Diabetes, Cardiovascular diseases and Stroke operational guidelines and literature from Indian Institute of Public Health-Hyderabad & Public Health Foundation of India.

After the 6-month training phase, an evaluation will occur. The evaluation will consist of theoretical and practical components which will be conducted using the developed questionnaire and the same set of trained public health experts respectively. The same tools would also be used for baseline collection. Both of these techniques will help assess the change in effective knowledge as well the practical skills about type 2 diabetes mellitus & associated complications. The detailed training plan is described below:

a.The trainers will teach the health workers about type 2 diabetes mellitus, its screening, complications and their screening. The trainers will be chosen based on prior knowledge of type 2 diabetes mellitus and prior teaching experience of evidence-based medicine in community health programs. Their willingness to be facilitators will also be an important factor for their selection.b.The trainers will participate in a 2-hour course^[36]^ focusing on type 2 diabetes mellitus and its complications. Two experienced faculty with extensive teaching experience will bear responsibility for the same. This training aims to provide the facilitators with sufficient skills and tools to conduct the training meetings successfully.c.The trainers will be provided with a detailed curriculum to be used in all meetings.d.An additional 2.5-hour session for trainers will be held three months into the academic detailing phase (i.e., after 3 meetings). This will support trainers during this phase of the intervention. They will also receive an ongoing email and phone support.e.The trainers will then impart training across a 6-month, 20-hour training to the health workers in the intervention group.f.The intervention will attempt to facilitate a change in the clinical competence of the health worker undergoing training.

#### Evaluation

2.4.3

The evaluation of the intervention package will help us understand the change in the competence of health workers in relation to type 2 diabetes mellitus and its complications. It will be conducted in the following manner for both the intervention & the control groups:

Paper basedOverall pre and post-test questionnaire, which will be derived from the diabetes knowledge test 2 of the Michigan University,^[33,34]^ the inputs from the physician/endocrinologist stakeholders, the assessment tools used by government training modules and evaluation tools developed by PHFI for diabetes training. This will help us understand the change in effective knowledge in the health workers in terms of type 2 diabetes mellitus, screening and complications.Practical BasedThis will be a practical test based on the training. It will help understand how effectively the training will be implemented by the health workers, when they are in contact with the diagnosed and undiagnosed patients. The scores of this assessment will be compared with the practical assessment carried out at the baseline.

Both the baseline and post training practical evaluation will be conducted by the same set of trained public health experts.

A combination of both paper-based and practical score will elucidate the change in the competence of the health workers.

Both the evaluation methods will be assessed according to objective parameters. It will ensure a comprehensive evaluation of all the components on which training will be provided (Table 1).

**Table 1 T1:**
[figure not shown]
A description of the training schedule of health workers in the intervention group^[28]^.

### Data collection, management & analysis

2.5

All the data will be collected from both the arms at pre-specified intervals. Pre and post- intervention data will be collected from the control arm. In the intervention arm, pre and post- training data will be collected, at the baseline and after the intervention is concluded. Hence evaluation will be conducted across both the groups at identical time points to obtain an accurate comparison of the training imparted. Qualitative and quantitative data will be collected during and after the intervention. The collected data will be coded and recorded in Microsoft Excel version 2020 (MS Excel). We will use MS Excel for summarizing the descriptive statistics.

These will be obtained from the socio-demographic characteristics, socioeconomic characteristics, lifestyle characteristics, type 2 diabetes screening, health center visits for physician follow-up and health center visits for medicine refill. We will use STATA for data analysis. The principal analysis strategy will be the use of linear mixed models using the R statistical package for computing. This approach provides a simple method to incorporate baseline values and the correlation of each participant over time (using a random effect). This model is more potent than the repeated measures analysis of variance. It can easily examine differences between the trial groups at all time points and can accommodate potential confounders. Subsequent adjustments will be made for potential confounding variables as necessary, such as baseline parameters that may vary between groups.

Data on the confounding factors including sex, literacy, distance from the health centre, marital status will be collected at baseline. Other socio-demographic details, socioeconomic status, and occupation will also be recorded at baseline.

Secondary contrasts will be used to examine differences from baseline for all other time points. However, these will be of exploratory interest only.

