#### Sample size calculations

2.3.2

The sample size is calculated based on the following formulae: 

Where

 to two-tailed at 5% significance level = 1.96

 to 80% power = 0.84d = effect size (estimated) = 0.5 (medium effect based on Cohen's d)m = cluster size = 30 (minimum number of health workers at one health center)ρ = intracluster correlation coefficient (estimated) = 0.03

we get n as 117 HWs per group. Adjusting the same for a dropout rate of 20%, 

 we get n as 147 per cluster group, i.e. 294 HWs across both arms. Therefore, 294 HWs across 8 clusters will be needed with 37 HWs across each cluster arm. Each cluster has 40–45 health workers and hence the sample size calculated is feasible for the study.

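### The principal mixed model describes a random effect for the participant but none for the health centre, which is the unit of randomisation

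*Protocol article*

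**What the plan says.** The Study design section calls this a "prospective, unblinded, parallel cluster randomized controlled trial". The Intervention phase and Sampling method sections agree that whole health centres, eight in all, are allocated to the two arms. Sampling method adds that centres are first formed into pairs on patient characteristics.

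Sample size calculations takes within-centre correlation into account, with "intracluster correlation coefficient (estimated) = 0.03" and "cluster size = 30 (minimum number of health workers at one health center", and arrives at 117 workers per arm before dropout.

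Data collection, management & analysis makes a linear mixed model the principal analysis. It explains the choice as a simple method to "incorporate baseline values and the correlation of each participant over time (using a random effect") and prefers it to repeated-measures ANOVA. Beyond that it mentions only potential confounders and baseline imbalances as adjustments. No section names a health-centre random effect, cluster-robust standard errors, a centre-level test or the pairs as part of the analysis.

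**The concern.** The design and the sample size treat the centre as the unit that carries the randomisation. The analysis text describes a model suited to an individually randomised longitudinal trial, in which the only correlation is between repeated scores of the same worker. An analyst who followed that description would treat workers as independently allocated.

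Workers at one centre share a setting and, in the intervention arm, training over the same six months. Differences between centres that have nothing to do with the training would then count as evidence for it. With only eight centres (four per arm if split equally), such differences do not average out well. At stake is the validity of the p-value and confidence interval for the main result.

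**Working it through.** **Inputs from Sample size calculations:** "to two-tailed at 5% significance level = 1.96"; z = 0.84 for 80% power; "effect size (estimated) = 0.5 (medium effect based on Cohen's d"); m = 30; ICC = 0.03; 20% dropout; 8 centres.

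**1. The plan's own figures reproduce.**
- Per arm without clustering: 2 × (1.96 + 0.84)² / 0.5² = 62.72.
- Design effect: 1 + (30 − 1) × 0.03 = 1.87.
- 62.72 × 1.87 = 117.3, which matches "we get n as 117 HWs per group".
- 117 / 0.8 = 146.25, rounded up to 147 per arm and 294 in total; 294 / 8 = 36.75, or about 37 per centre.

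The sample size therefore rests on a design effect of 1.87, which the described model does not carry over.

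**2. Post-score comparison with no centre term.** The standard error is too small by √1.87 = 1.37. The actual two-sided type I error is 2 × [1 − Φ(1.96 / 1.367)] = 15.2%, and a nominal 95% interval covers 84.8%. The same formula gives:
- At ICC 0.03: 17.3% for m = 36.75 (design effect 1 + 35.75 × 0.03 = 2.07), 18.3% for m = 40 and 19.8% for m = 45. The document says 40 to 45 workers are available per centre.
- At m = 30, for assumed ICCs: 8.4% (0.01), 11.9% (0.02) and about 21% (0.05).

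**3. Models that use both time points.** A participant effect removes whatever part of the centre effect is constant over time, so the formula in step 2 does not apply directly. The check was a simulation under no true effect: 6,000 runs, 4 + 4 unpaired centres of 30, ICC 0.03 at each time point. The within-worker correlation of 0.5 is an assumption, as is the split of the centre effect into stable and time-varying parts.

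| Share of centre variance constant over time | Post score only | Pre/post change (participant effect only) | Baseline-adjusted | Centre-level t-test, 6 df |
|---|---|---|---|---|
| All | 15.3% | 5.0% | 8.1% | 4.9–5.0% |
| Half | 15.3% | 14.8% | 15.3% | 4.9–5.2% |
| None | 15.3% | 23.7% | 20.5% | 4.6–4.9% |

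Simulation error near 5% is √(0.05 × 0.95 / 6000), about 0.3 percentage points. With a within-worker correlation of 0.3 and no stable part, the change contrast gave 18.9% and the baseline-adjusted comparison 16.7%.

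**4. Power when centre is respected.** At d = 0.5, ICC 0.03 and no baseline adjustment, SE = √(2 × design effect / n per arm).
- n = 117 (29.25 per centre, design effect 1.8475): SE = 0.178, ratio 0.5 / SE = 2.81. Power is 80% by the normal approximation and 65% by the t distribution on 6 df.
- n = 147 (36.75 per centre, design effect 2.0725): SE = 0.168, ratio 2.98. Power is 85% and 70% respectively.
- With a matched analysis of four pairs (3 df), the corresponding figures are about 49% and 53% if the matching removes no between-centre variance.

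**The case against.** Three points can be made in the plan's favour.

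First, a reader might infer that the model has a participant effect only and that a centre effect has been ruled out. The document does not say so. The sentence gives a reason for using mixed models; it is not a model specification, and a linear mixed model can hold a centre term. The authors clearly know the trial is clustered. This stands: the text is silent on a centre term.

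Second, this is a journal article. The full random-effects structure and the choice of degrees of freedom are commonly left to the analysis plan, so the absence of a small-sample method is not a fault in itself. This stands too. It does not remove the point, because the article does describe a random effect, assigns it to the participant, and so conflicts with the clustering in its own design and sample-size sections.

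Third, a reader might take 15% as the error rate of the planned analysis, or conclude that the p-values must be too optimistic. Neither follows. The 15% belongs to a post-score comparison in which ICC 0.03 applies to the analysed outcome. The article describes a model with baseline values. For a pre/post contrast with wholly stable centre effects the error rate stays at 5%. The document does not give the centre-by-time variation, nor does it say whether the ICC refers to the raw score, the adjusted score or the change.

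**Conclusion.** The point holds as an inconsistency to be corrected before analysis: centres are randomised and the sample size is inflated for centre, but the principal model as described names no centre effect.

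If it is fitted that way, the type I error is about 15% for a post-score comparison at the plan's ICC and m = 30, and about 17% at 37 per centre. It ranges from about 5% to 24% for a pre/post contrast and from about 8% to 21% for a baseline-adjusted comparison. The last two ranges rest on an assumed within-worker correlation of 0.5 and on unpaired allocation of four centres per arm. Effective pairing would change the between-centre variance and hence these figures. The conclusion that a centre term is needed does not depend on which value applies, since nothing in the document supports assuming that centre effects are wholly stable over time.

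**What to change.** State the primary model as the post-intervention competence score on arm, adjusted for the worker's baseline score, with a random intercept for health centre. If both time points are kept as outcomes, include centre and centre-by-time random effects as well as the participant effect.

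Test the arm effect with Kenward-Roger or Satterthwaite degrees of freedom, or with a t-test on centre summaries. State whether the pairing described under Sampling method is kept in the analysis: about 6 df unmatched, 3 df matched.

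The cost in wording is about one paragraph plus the added centre term or terms, and no further data are needed. The statistical cost is real. Confidence intervals widen, and power on 6 df without baseline adjustment is about 65% (117 per arm) to 70% (147 per arm) rather than the stated 80%. Baseline adjustment may recover some of this, but the document gives no figure from which to say how much. The power statement should be revised together with the model.
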